## Abstract

**Background:**

As the strongest prodromal marker of α-synuclein-specific neurodegeneration, idiopathic REM sleep behavior disorder (iRBD) is becoming a focus of interest in disease-modifying therapy. Idebenone has been widely portrayed as a potent antioxidant targeting mitochondrial dysfunction. Previous study has identified the effect of idebenone on Parkinson's disease with promising outcomes by regulating mitophagy. A novel indication of idebenone should be highlighted in iRBD population.

**Methods:**

The EITRS study is a randomized, double-blind, multi-center clinical study assessing the efficacy and safety of idebenone in the treatment of iRBD into synucleinopathies. One hundred forty-two patients (aged 40–75 years old) with clinically diagnosed iRBD are planned to be recruited with 80% statistical power and randomly assigned to idebenone (30 mg each time, three times a day) or matching placebo orally for 5 years. The assessment of rating scales, blood testing and neuroimaging examinations will be conducted at baseline, the 1st, 3rd and 5th year of follow-up. The primary efficacy endpoint is the 5-year conversion rate in patients with iRBD. The secondary endpoint is the safety and tolerability of idebenone in the treatment of iRBD. The study has been launched in July 2020.

**Discussion:**

This is the first prospective study designed to identify the efficacy and safety of idebenone on the treatment of iRBD into synucleinopathies. The current results are expected to promote the development of evidence-based recommendations for the management of patients with iRBD. Furthermore, we hope to provide insights on a possible disease-modifying approach with robust evidence.

**Trial Registration:**

Clinicaltrials.gov, identifier: NCT 04534023.

## Background

Rapid eye movement (REM) sleep behavior disorder (RBD) is a parasomnia characterized by dream enactment behaviors and the loss of physiological muscle atonia during REM sleep (1). RBD has been categorized into idiopathic RBD (iRBD) and symptomatic forms, the latter of which is acknowledged as a precursory sign of α-synucleinopathies, including Parkinson's disease (PD), dementia with Lewy bodies (DLB), and multiple system atrophy (MSA), etc. (2). α-synucleinopathies are a group of neurodegenerative disorders characterized by aggregates of α-synuclein in neurons and glia, in the form of Lewy bodies, Lewy neurites, neuronal cytoplasmic inclusions, and glial cytoplasmic inclusions (3). More than 80–90% of iRBD patients ultimately develop a clinically defined neurodegenerative disease over longitudinal follow-up (4). Consequently, iRBD is considered as a recognizable preclinical state to enable the identification of individuals at risk of neurodegeneration (5). However, the pathogenesis and the potential mechanism still need investigation with little understanding of the reliable biomarkers of phenoconversion, which hinders the early diagnosis and intervention. Recent animal models and brain imaging researches revealed the degeneration of the core brain stem circuits controlling REM sleep in RBD pathology (6, 7). The initial REM sleep atonia loss (RSWA) and RBD symptoms accord with the pathological progression of Lewy body in PD which begins in the medulla and pons (8–10). It is speculated that α-synuclein could begin in the caudal brain stem affecting REM sleep circuits and progressively propagate to substantia nigra and other brain region (11). Besides, iRBD patients frequently exhibit specific neurodegenerative biomarkers, including: (1) clinical symptoms of hyposmia, constipation, orthostatic hypotension, cognitive decline, and gait initiation abnormalities; (2) structural or functional magnetic resonance imaging (MRI) signifying decreased nigrostriatal putamenal dopaminergic uptake, altered neuromelanin signal intensity and cortical thinning, as well as the brain glucose metabolism measured by ^18^F-FDG PET positron emission tomography (^1^8F-FDG PET) and dopamine transporter deficit by ^123^I-N-ω-fluoropropyl-2β-carbomethoxy-3β-(4-iodophenyl) nortropane single-photon emission computed tomography (^123^I-FP-CIT SPECT); (3) neurophysiological markers such as electroencephalographic slowing, etc (5, 12, 13). The signs may be important predictors for impendent phenoconversion, while the application should be integrated considering higher sensitivity and specificity.

The management of iRBD is principally focused on physical protection and pharmacotherapy (1, 14). Clonazepam and melatonin are widely prescribed in the clinical practice as grade B recommendation (15). Clonazepam can significantly reduce the occurrence of RBD behavior and trauma, whereas it should be applied with caution on patients with dementia, gait abnormalities or obstructive sleep apnea syndrome (16). The administration should also be monitored strictly especially on patients with neurodegenerative diseases or abnormal liver function. Long-term application may contribute to excessive daytime sedation, movement disorders, blurred consciousness, amnesia, etc (1). Instead, melatonin has a much safer profile with fewer and milder side effects. Its efficacy has been corroborated in the treatment of iRBD with or without concurrent DLB, PD or MSA (17, 18). The dose-related adverse reactions of melatonin most commonly include morning headache, daytime sleepiness, delusions and hallucinations (17). Nonetheless, evidence of both the medications above is still insufficient to validate their utility on phenoconversion in the prodromal stage.

Mitochondrial dysfunction has been verified predominately responsible for dopaminergic neuron degeneration, which can be promising as a novel therapeutic target (19). Idebenone is a potent antioxidant and inhibitor of lipid peroxidation that is capable of stimulating mitochondrial electron flux and cellular energy production, which ensures the integrity of mitochondrial function and structure (20). Idebenone may exert a protective effect against neuroinflammation and microglial activation in PD. Complementary therapy with idebenone addressed motor and non-motor issues and mitigated the pathology of PD in animal and cell models (21–25). However, the extensive mechanisms need better interpretation and solid evidence is warranted to quantify the effectiveness and safety in clinical practice. Herein, we describe the design and rationale of a prospective clinical trial to identify whether idebenone can reduce the conversion rate or postpone the onset of neurodegeneration effectively in the treatment of iRBD.

## Methods

### Study aims

The primary aim of the study is to investigate the 5-year conversion rate of α-synucleinopathies in iRBD patients treated with idebenone. The secondary aim is to clarify the safety and tolerability of idebenone in the treatment of iRBD patients over longitudinal follow-up.

### Study designs

EITRS is a randomized, double-blind, multi-center clinical study with two parallel arms in 1:1 ratio to evaluate the efficacy and safety of idebenone in patients with iRBD compared with placebo. The total study duration of 6 years comprises a 1-year enrollment period and a 5-year intervention period. One hundred forty-two eligible participants will be allocated to idebenone or placebo group randomly and equally after baseline assessment. Follow-up evaluations will be conducted at the 1st, 3rd and 5th years of treatment in any of the three centers to detect the disease progression. Routine blood testing and liver function will be monitored every 6 months during the administration. Participants, investigators and statisticians are masked to the allocation code. The flowchart of the trial is outlined in Figure 1. The EITRS study is registered with ClinicalTrial.gov (Register Number: NCT 04534023).

**Figure 1 F1:**
[figure not shown]
Flowchart of study design.

### Patients and study sites

In total, 142 outpatients were recruited from the department of Neurology of three centers in Shanghai, Suzhou and Wuhan: Ruijin Hospital affiliated to Shanghai Jiaotong University School of Medicine, the Second Affiliated Hospital of Soochow University and Union Hospital, Tongji Medical College, Huazhong University of Science and Technology. Among them, Ruijin Hospital is the leader of EITRS, in charge of patient enrollment, quality control and ethical problems. Patients were enrolled between July 2020 (study start date) and July 2021; the study end date (last patient completed the study) was July 2026. The inclusion and exclusion criteria are depicted as follows.

### Inclusion criteria

Male or female, aged 40–75;The diagnosis of RBD was confirmed by polysomnography (PSG) according to standard criteria published by the American Academy of Sleep Medicine in the International Classification of Sleep Disorders (ICSD) III (26);Patients voluntarily participated in this study and signed informed consent with good compliance.

### Exclusion criteria

PSG-confirmed sleep apnea hypopnea syndrome, which includes but not limited to obstructive sleep apnea syndrome (apnea/hypopnea index >5) (26);Patients with symptoms including bradykinesia, myotonia, tremor or posture instability;Previous history of sudden withdrawal of sedative or psychotropic drugs prior to the onset of the symptoms;Previous history of neurological diseases such as cerebral hemorrhage, cerebral infarction, brain trauma, brain tumor or central nervous system infection;Previous history of sleep disorders or seizure;Alcohol or drug dependence (addiction).

### Endpoint criteria

Patients finish 5-year idebenone treatment;Patients develop overt α-synucleinopathies according to the diagnostic criteria. The definition of α-synucleinopathies in the endpoint contains three most common types: PD, DLB and MSA.

### Discontinue criteria of intervention

Severe liver and kidney function abnormality associated with the intervention (transaminase increase more than twice of the normal value);Severe blood testing abnormality: red blood cell, hemoglobin, white blood cell or platelet count <50% of the lower normal limit, or more than twice the upper normal limit;Severe allergic reactions or arrhythmias: severe hypertension (blood pressure > 220/120 mmHg) or hypotension (blood pressure < 80/60 mmHg) caused by intervention; or severe arrhythmias (heart rate < 50 beats/min, heart rate > 140 beats/min or atrial fibrillation) and sinus arrest; or respiratory disorder (oxygen saturation < 85%);Consciousness disorders: coma, delirium or convulsions.

### Discontinue/withdraw criteria of patients

Pregnant;Poor compliance to the protocol;Serious complications or other severe diseases happen during the administration and the continuation shows little benefits;Significant disease progression and the discontinuation is necessary after evaluation;Meet the exclusion criteria (newly or already confirmed);Unable to receive the intervention as scheduled.

Participants will be included in the final statistical analysis if they accomplish three courses of treatment and evaluation, otherwise will be excluded.

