### Intervention and follow-up

During the 5-year treatment, patients will undergo oral administration of idebenone or placebo with a dosage of 30 mg each time, three times a day. Given idebenone is prescribed conventionally for cerebral infarction, cerebral hemorrhage, and atherosclerosis sequelae caused by brain dysfunction, the optimal dosage is recommended by the instruction of idebenone (30 mg per tablet, Shenwei, Qilu Pharmaceuticals, China). We also deliberated the administration according to preliminary literatures and clinical trials in the use of neurodegenerative disorders (27–29). Therefore, the dosage is fixed without setting dose gradient as control groups. The drug will be kept by blinded nurses, and distributed to patients according to the code. Routine blood testing and liver function will be monitored every 6 months during the administration. Once serious side effects occur, such as leukopenia, liver function damage or severe allergic reaction, participants should discontinue or withdraw from the trial. The follow-up evaluations of patients include the assessment of rating scales, blood testing and neuroimaging examinations. Movement Disorder Society-Unified Parkinson's Disease Rating Scale (MDS-UPDRS), Mini-Mental State Examination (MMSE), Montreal Cognitive Assessment (MoCA), Sniffin' Sticks test-16 (SS-16), 17-Item Hamilton Rating Scale for Depression (HAMD-17), Non-Motor Symptom Questionnaire (NMSQ) and Scales for Outcomes in Parkinson's Disease-Autonomic questionnaire (SCOPA-AUT) is used to quantify the progression of motor and non-motor symptoms. In view of the favorable improvement on neurodegenerative disease of idebenone, it is speculated that idebenone might ameliorate RBD symptoms as well (30). Therefore, we use REM sleep behavior disorder screening questionnaire (RBDSQ) to identify the influence. Plasma exosome-synuclein levels will be tested to provide convictive biomarkers for neurodegeneration. Several inflammatory cytokines and chemokines (interleukin-6 (IL-6), IL-8, IL-10, tumor necrosis factor-α (TNF-α), TGF-β, C-X-C motif ligand (CXCL) 12, C-X3-C motif ligand 1 (CX3CL1), C-C motif ligand (CCL) 3, CCL15 and CCL20) will be measured based on our previous investigation (31). The SNCA methylation will also be analyzed by bisulfite sequencing (32, 33). In addition, according to our previous publications, functional connectivity impairment and increased free water in the posterior substantia nigra are indicative imaging markers for phenoconversion (34–36). PET/MRI can also provide supplementary evidence for dopaminergic neurodegeneration, which is necessary for the participants in the follow-up evaluation.

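### Poor compliance, missed treatment, progression and new motor signs are grounds for removing the patient, not only the drug, so conversion outcomes needed for intention-to-treat may be lost

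*Protocol article*

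**What the plan says.** The Methods of the protocol article contain two stopping lists. The first, headed "Discontinue criteria of intervention", covers laboratory, cardiovascular, allergic and neurological safety limits. The second comes under a heading that refers to discontinuing or withdrawing patients. Among other reasons it lists "Poor compliance to the protocol" and "Significant disease progression and the discontinuation is necessary after evaluation;Meet the exclusion criteria (newly or already confirmed);Unable to receive the intervention as scheduled".

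Four other places bear on how the second list works:

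- **Exclusion criteria:** these include "Patients with symptoms including bradykinesia, myotonia, tremor or posture instability". A patient who develops such signs after randomisation newly meets an exclusion criterion.
- **Endpoint criteria:** one route to the endpoint is "Patients develop overt α-synucleinopathies according to the diagnostic criteria", defined as PD, DLB or MSA. A patient who is already diagnosable therefore counts as converted.
- **Intervention and follow-up:** after serious side effects, "participants should discontinue or withdraw from the trial". This can be read as leaving the drug or leaving the trial.
- **Timing of visits:** the abstract places assessments at "the 1st, 3rd and 5th year of follow-up", whereas Study designs counts the same visits in years of treatment.

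The primary outcome is conversion at 5 years. Sample size and statistical analysis specifies intention-to-treat, with a Cox model and Kaplan-Meier curves.

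**The concern.** Having a separate drug-stopping list implies that the second list removes the person. If so, patients who take the drug poorly, miss treatment, progress or develop motor signs may have no later conversion assessment. Putting every randomised patient in the analysis set does not repair this, because the outcome was never observed. That makes the point separate from the sentence in the same section that restricts the final analysis to those who complete three courses.

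Cox and Kaplan-Meier both assume that censoring carries no information about the outcome. Progression and new bradykinesia or tremor are plausibly linked to imminent conversion, so censoring at that moment may break the assumption. The exposed group is patients with signs or progression who do not yet meet diagnostic criteria. After year 1 the visits are two years apart, so a patient removed around year 3 could miss the only remaining conversion visit.

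**Working it through.** **Inputs from Sample size and statistical analysis:** 5-year conversion 47% on placebo and 25% on idebenone, 1:1 allocation, 71 per arm, two-sided 5% level, 80% power, 5% drop-out. Assumed here: exponential conversion times, and every loss share other than 5%.

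**Reproducing the plan's figure.** HR = ln(0.75)/ln(0.53) = 0.453. Expected events without loss = 71 × (0.47 + 0.25) = 51.1. Schoenfeld power = Φ(√events × |ln HR|/2 − 1.96) = 0.808. With 5% drop-out treated as exponential censoring, the events are 49.9, power is 0.799 and the N for 80% power is 142.5. This agrees with the stated 142.

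**Loss unrelated to conversion (share of all patients).**

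| Share lost | Events | Power |
|---|---|---|
| 5% | 49.9 | 0.799 |
| 10% | 48.7 | 0.789 |
| 20% | 46.3 | 0.768 |

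**Loss confined to would-be converters, equal share *a* in both arms, censored just before diagnosis.** The observed hazard in each arm is multiplied by (1 − a), so the HR stays at 0.453. Kaplan-Meier then estimates 1 − 0.53^(1−a) and 1 − 0.75^(1−a), and events are 51.1 × (1 − a).

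| a | Placebo | Idebenone | Events | Power (Schoenfeld) | Power (log-rank simulation, 20,000 runs) |
|---|---|---|---|---|---|
| 0 | 47.0% | 25.0% | 51.1 | 0.808 | 0.79 |
| 10% | 43.5% | 22.8% | 46.0 | 0.766 | 0.76 |
| 20% | 39.8% | 20.6% | 40.9 | 0.716 | 0.70 |
| 30% | 35.9% | 18.2% | 35.8 | 0.658 | 0.64 |

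At a = 20% the patients lost are 71 × 0.47 × 0.2 = 6.7 on placebo and 71 × 0.25 × 0.2 = 3.6 on idebenone. With no drug effect and equal loss, the simulated type I error was 0.048 to 0.052.

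**Worst-case illustration: no drug effect (47% in both arms), loss confined to would-be converters and different by arm.** With 20% lost on idebenone and 10% on placebo, HR = 0.8/0.9 = 0.889. Events = 71 × 0.47 × (0.8 + 0.9) = 56.7. The mean of the test statistic is √56.7 × |ln 0.889|/2 = 0.44, which gives a two-sided type I error of 0.073 (simulated 0.072). The reverse pattern gives HR = 0.9/0.8 = 1.125.

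**The case against.** The strongest reply is that the article never says assessments stop. It is a condensed report, and off-drug follow-up is often left to the full protocol. The heading is loose, and several items are worded about treatment. The progression item applies only when stopping is judged necessary after evaluation. No passage says that motor signs lead to withdrawal and not to diagnostic work-up. Diagnosed converters count as events, and the Discussion sends diagnoses to independent expert review. The wording on serious side effects does not concern the four reasons at issue.

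The loss shares are also assumed. The planned 5% drop-out is about 7 of 142 patients. A 10% share of would-be converters is about 5 patients (3.3 + 1.8) and fits within that, but 20% (about 10) and 30% (about 15) exceed it. Blinding makes equal loss plausible, and equal loss leaves the hazard ratio unbiased.

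Much of this stands as a limit on size. The motor-sign route is an inference, the exposed group may be small, and no figure in the article says how often it would arise. It does not remove the point. A list for patients, set apart from a list for the drug, is a stated rule and not a silence. Followed as written, it can end assessment for people close to converting. If the wording was meant to cover drug only, it is still loose enough for three centres to apply it differently.

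**Conclusion.** The concern holds and should be fixed. As written, the patient-level criteria can remove randomised patients from conversion assessment for reasons tied to treatment adherence and, by inference, to early conversion itself. Confidence is medium because the heading is loose.

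The size and direction are not known from the document. Loss unrelated to conversion is nearly harmless. Equal loss among would-be converters leaves the hazard ratio and type I error intact, but it understates both conversion rates and costs power: 0.81 falls to 0.77, 0.72 or 0.66 at shares of 10%, 20% or 30%. Only loss that differs by arm biases the hazard ratio, and the 0.89 and 1.12 figures are illustrations, not forecasts. All these results rest on exponential conversion times and on withdrawn patients being censored.

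**What to change.** Amend the patient discontinuation/withdrawal criteria and the matching sentence in Intervention and follow-up as follows:

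- The listed reasons end or pause study drug only. The clinical grounds for stopping drug do not change.
- Every randomised patient stays blinded and on the year 1, 3 and 5 conversion assessments, counted from randomisation, until conversion or year 5, unless consent to follow-up is withdrawn.
- Patients with progression or new bradykinesia, tremor or postural instability go to conversion assessment and the expert review described in the Discussion, and are not withdrawn.
- Imaging, described as "which is necessary for the participants in the follow-up evaluation", or any other procedure is omitted where unsafe, for example in pregnancy. The clinical conversion assessment is kept.
- Patients already withdrawn are re-contacted, where consent allows, to establish conversion status and date.

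The cost is one amendment, the re-contact work and continued visits for patients off drug, some of whom will decline. Enrolment ran to July 2021 and the stated study end is July 2026, so data already missed may be only partly recoverable.

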### Sample size and statistical analysis

The 5-year conversion rate of participants treated with idebenone is expected to decrease from 47% in the placebo group to 25%. The idebenone and placebo group are randomized at a ratio of 1:1, and a 5% drop-out rate is considered throughout the study. We estimated that 71 patients would be needed in each treatment group to allow for a power of 80% at two-sided α-level of 5%. In total, 142 patients are projected to be enrolled.

Statistical analysis will be performed using SPSS 27.0, STATA 17.0 and GraphPad Prism 9.4.0. Data will be analyzed on an intention-to-treat basis using two-sided tests with *p* < 0.05 considered significant. Continuous variables will undergo normality test as well as ANOVA test for inter-group comparison. Categorical variables will be compared using Chi-square test, Fisher's exact test or Wilcoxon rank-sum test. To assess the five-year conversion rate from iRBD diagnosis to clinically diagnosed synucleinopathies between patients treated with idebenone and placebo, we estimated the hazard ratio (HR) using a Cox proportional hazards model. Kaplan-Meier method will be applied to estimate median progression-free survival (PFS) and corresponding 95% confidence interval (CI) and survival curves will be plotted.

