In this paper, we outlined our rationale and design of the EITRS study. The EITRS study is a randomized, double-blind, multi-center clinical study is to identify the efficacy and safety of idebenone in the treatment of iRBD into synucleinopathies initially. Three centers participate in the trial and the first patient has been recruited into the study in July 2020. The study is leaded by Ruijin Steering Committee. The Steering Committee members and principal investigators of each center are in charge of the ethics and patient safety. They will have a face-to-face or online meeting to supervise the status and progress of the trial. The diagnosis of iRBD and α-synucleinopathies will be reviewed by independent experts in each center and steering committee. The sponsor of the EITRS trial is the Clinical Research Center, Shanghai Jiao Tong University School of Medicine. The results are expected for publications in 2026.

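### New motor signs meet an exclusion criterion and so a withdrawal criterion: as written, a patient can be removed before PD or MSA can be diagnosed as the endpoint

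*Protocol article*

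**What the plan says.** Four statements in the protocol article interact.

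- **Withdrawal.** Discontinue/withdraw criteria of patients lists as one reason: "Meet the exclusion criteria (newly or already confirmed". This list concerns patients. It is separate from the preceding list of reasons to stop the intervention, which is not in question here.
- **Exclusion.** Exclusion criteria includes: "Patients with symptoms including bradykinesia, myotonia, tremor or posture instability". No severity, duration or diagnosis is required.
- **Endpoint.** Endpoint criteria requires: "Patients develop overt α-synucleinopathies according to the diagnostic criteria". It adds: "The definition of α-synucleinopathies in the endpoint contains three most common types: PD, DLB and MSA".
- **Analysis.** The sentence after the withdrawal list reads: "Participants will be included in the final statistical analysis if they accomplish three courses of treatment and evaluation, otherwise will be excluded". Sample size and statistical analysis says instead: "Data will be analyzed on an intention-to-treat basis".

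Two other places bear on intent. In Intervention and follow-up, the battery that includes the MDS-UPDRS "is used to quantify the progression of motor and non-motor symptoms". The Discussion says: "The diagnosis of iRBD and α-synucleinopathies will be reviewed by independent experts in each center and steering committee".

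**The concern.** The exclusion criterion is met by symptoms; the endpoint is met only by a diagnosis. Any interval between first motor sign and diagnosable PD or MSA (or DLB with motor onset) is, on the text, a state that calls for withdrawal. A patient on the expected path to the endpoint can therefore be taken out just before reaching it. Full evaluations come only at years 1, 3 and 5, so a patient withdrawn for an isolated tremor at year 1 or 3 has no later scheduled evaluation at which to be diagnosed.

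These are the patients most likely to convert next, so their removal is not like random drop-out and the 5% drop-out allowance does not cover it. If they are censored, the Cox model's assumption of non-informative censoring fails. If they are excluded, the comparison is no longer between the randomized groups. Equal loss in the two arms mainly costs events and power. Unequal loss also biases the hazard ratio: if idebenone eased early motor signs, placebo would lose more of its converters and the benefit would be understated.

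**Working it through.** **Inputs from the protocol article (Sample size and statistical analysis).** Five-year conversion 47% on placebo and 25% on idebenone; 1:1 allocation; 71 per arm, 142 in total; 80% power; two-sided α of 5%; 5% drop-out; Cox model for the hazard ratio (HR).

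**Assumption.** Let f be the share of eventual converters withdrawn for motor signs before diagnosis. The document gives no value, so 10%, 25% and 50% are used as an illustrative range.

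**The plan's own figure.** Under exponential conversion times, HR = ln(0.75)/ln(0.53) = 0.453. Schoenfeld's formula needs 4 × (1.960 + 0.842)² / (ln 0.453)² = 50.1 events. With 5% drop-out over five years as exponential censoring, the mean event probability is 0.352, so N = 50.1/0.352 = 142.5. The stated 142 is reproduced, with power 79.9%.

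**1. Equal f, withdrawn patients censored** (this assumes conversion follow-up ends at withdrawal). Mean conversion is (0.47 + 0.25)/2 = 0.36. Events = 142 × 0.36 × (1 − f). Power = Φ(√(events/4) × |ln 0.453| − 1.96). The 5% drop-out columns use 67.45 per arm (71 × 0.95).

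| f | Events | Power | Events, 5% drop-out | Power, 5% drop-out |
|---|---|---|---|---|
| 0 | 51.1 | 0.808 | 48.6 | 0.788 |
| 10% | 46.0 | 0.766 | 43.7 | 0.744 |
| 25% | 38.3 | 0.688 | 36.4 | 0.666 |
| 50% | 25.6 | 0.516 | 24.3 | 0.496 |

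**2. Equal f, withdrawn patients excluded from the analysis.** Observed rate = p(1 − f)/(1 − pf), with 71(1 − pf) patients left per arm. Power is for a two-proportion test with pooled null variance and no further drop-out. Implied HR = ln(1 − idebenone rate)/ln(1 − placebo rate).

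| f | Placebo | Idebenone | Power | Implied HR |
|---|---|---|---|---|
| 0 | 0.470 | 0.250 | 0.786 | 0.45 |
| 10% | 0.444 | 0.231 | 0.757 | 0.45 |
| 25% | 0.399 | 0.200 | 0.702 | 0.44 |
| 50% | 0.307 | 0.143 | 0.570 | 0.42 |

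**3. Unequal f, withdrawn patients censored.** Approximate observed HR = 0.453 × (1 − f on idebenone)/(1 − f on placebo).

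- 30% placebo, 20% idebenone: 0.453 × 0.80/0.70 = 0.518.
- 20% placebo, 30% idebenone: 0.453 × 0.70/0.80 = 0.396.

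A simulation with exponential conversion and withdrawal assumed one year before diagnosis (6,000 trials) gave median Cox HRs of 0.508 and 0.389, close to the approximation.

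**The case against.** The strongest reply is about meaning. *Newly* can be read with *confirmed*: the item would then cover an eligibility failure discovered late, which suits the several exclusion criteria that are history items. The same list also has a conditional item for significant disease progression, which would be largely redundant for motor progression if any new tremor already forced withdrawal. The endpoint definition, the repeated motor scales and the expert diagnostic review all suggest that the investigators meant to follow motor signs, not to remove patients for them.

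This makes a drafting overlap likely, but it does not repair the text. A tremor first confirmed on study still meets the criterion, and a conditional progression item does not override a separate unconditional one.

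Two further points stand in part. First, the sentence that removes incomplete patients from the analysis conflicts with intention-to-treat for every withdrawal reason, so calculation 2 depends on that wider contradiction. But intention-to-treat alone would not settle the matter, because it cannot supply a conversion that was never observed. The article does not say outright that conversion follow-up stops at withdrawal, but nothing says that it continues. Second, the sizes rest on an assumed f. Under equal loss with censoring the HR is roughly unchanged; under equal exclusion it moves only slightly (0.45 to 0.42 at f = 50%). The scenario in which placebo loses more converters makes the result conservative.

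That the full protocol might say more is a weaker reply, since this is a stated rule at odds with a stated endpoint and not an omitted detail.

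**Conclusion.** The concern holds: the withdrawal item is wrong as written and should be fixed. Applied literally, it removes likely PD and MSA converters before the endpoint can be recorded.

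The size depends on how many converters would be caught, which the document does not say. Because power is set at only 80%, even a 10% loss with censoring takes it below target (77%, or 74% with the planned drop-out), and a 50% loss leaves about half. A ten-point imbalance in loss at the levels shown moves the HR from 0.45 to about 0.52 or 0.40.

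The scope is limited. Patients already diagnosable when the signs are first seen count as endpoints, and DLB that begins with cognitive decline need not be affected. If sites apply the item only to eligibility errors, no converters are lost this way. Confidence is medium for that reason.

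**What to change.** - Exempt the motor-symptom criterion from the post-randomization withdrawal item. Leave the item in place for the other criteria, such as a new seizure or stroke.
- State that new motor signs trigger endpoint assessment and the expert diagnostic review already described in the Discussion.
- For any item on the patient withdrawal list that stops study drug, continue the year 1, 3 and 5 conversion assessments unless consent is withdrawn, and keep the patient in the primary analysis. The sentence that limits the analysis to patients who complete treatment and evaluation must then be removed or amended to match.
- Enrollment was planned to close in July 2021 and the study to end in July 2026, so for anyone already withdrawn for motor signs, seek conversion status and report it.

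The cost is protocol wording, attendance at visits already scheduled by patients who stop study drug, and tracing any patients already withdrawn. No change in sample size is needed.
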